### Inclusion and exclusion criteria

The inclusion criteria were as follows: (1) nonsmoking female patients who were 18–50 years old with a planned laparoscopic appendectomy or cholecystectomy from October 1, 2021, to October 1, 2022; (2) American Society of Anaesthesiologists (ASA) classification I–III; (3) no analgesic/sedative medication was used within 24 h before surgery; (4) no serious endocrine, cardiovascular and respiratory diseases before surgery; (5) no mental abnormality; and (6) provision of signed informed consent.

The exclusion criteria included patients who (1) had an allergic history of anaesthetic drugs or contraindications of esketamine, nonsteroidal anti-inflammatory drugs or dexmedetomidine; (2) had mental disorders, preoperatively screened using a neuropsychiatric inventory; (3) had poorly controlled or untreated hypertension with resting arterial pressure over 180/100 mmHg; (3) had addiction or dependence on opioid or hypnotic drugs; and (4) had respiratory infection or asthma before surgery.

Patients who were enrolled but met one of the following criteria were excluded from the study: (1) incomplete case report form or lost to follow-up and failed to make an effective and safety assessment, (2) change of anaesthesia method due to unexpected incident or surgery requirement during the surgery, (3) operation could not be continued due to unexpected incident during the surgery and (4) other diseases post-surgery required urgent treatment.

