### Dropout criteria

The dropout criteria are as follows: (1) withdrawal of consent by the participants or their legal representative and (2) loss to follow-up.

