### Primary outcome

The primary outcome was the incidence of PONV 3 days after surgery. PONV is defined as a spectrum incorporating some combination of nausea, vomiting and/or retching in the postoperative period. Nausea and vomiting scales are also used to grade PONV severity [19]. The dosage and frequency of use of postoperative antiemetic drugs (metoclopramide or 5-hydroxytryptamine antagonist) were also recorded for analysis.

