### Sample size calculation

The sample size was calculated with PASS 15.0 (Number Cruncher Statistical Software, LLC, Kaysville, UT, USA). The hypothesis of this trial is that esketamine could be associated with fewer side effects of PONV than opioid anaesthesia. With *α* = 0.05 and a power of 90%, we assumed that esketamine anaesthesia may reduce the PONV rate from 37.3 to 20% according to a study by Ziemann-Gimmel et al. [25]; thus, a sample size of 139 for each group would be needed. According to previous studies, the general incidence of vomiting after surgical anaesthesia is approximately 30%, while the incidence of nausea is approximately 50% [26–28]. Therefore, proportions of 37.3% and 20% of PONV of patients in the F group and E group, respectively, were used to calculate the sample size.

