### Statistical analysis

Statistical analyses will be performed using SPSS 25.0 (IBM SPSS Statistics, Armonk, NY). An intention-to-treat (ITT) approach will be used to analyse the data. All data will be checked for normal distribution using the Kolmogorov test. For normally distributed data, continuous variables will be analysed using the independent Student’s *t* test, and the variables will be presented as the mean ± standard deviation (SD). Nonnormally distributed data will be compared using the Mann‒Whitney *U* test where appropriate, and data will be presented as the median and interquartile range (IQR). For categorical variables, cross-tabulation and the Pearson chi-squared test will be applied, and variables will be categorized as numbers and/or percentages of the total. A logistic regression model will be applied to detect any potential confounding factors. To compare the continuous measurements of HR and NIBP between the groups, the area under the curve (AUC) for each value will be calculated over the different measurement time points during the procedure. To compare the continuous measurements of HR and NIBP between the groups, the area under the curve (AUC) for each value will be calculated over the different measurement time points during the procedure. Missing data are neglected or multiple imputation will be used when > 40% and identified as missing, not at random. A *p* value < 0.05 with two tails will be considered statistically significant.

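### The missing-data rule neglects missing outcomes up to 40% and reserves multiple imputation for data identified as missing not at random, a trigger that cannot be operated and where standard imputation is not valid

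*Protocol article*

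**What the plan says.** All of the following is in the protocol article.

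- Statistical analysis, on missing data: "Missing data are neglected or multiple imputation will be used when > 40% and identified as missing, not at random".
- Statistical analysis, on the analysis principle: "An intention-to-treat (ITT) approach will be used to analyse the data".
- Inclusion and exclusion criteria: the list of reasons for removing patients after enrolment begins with "incomplete case report form or lost to follow-up and failed to make an effective and safety assessment".
- Dropout criteria: "withdrawal of consent by the participants or their legal representative and (2) loss to follow-up". Loss to follow-up is therefore both a reason for exclusion and a type of dropout.
- Primary outcome: "The primary outcome was the incidence of PONV 3 days after surgery", a yes/no outcome. The same section says that antiemetic dose and frequency are recorded.

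The missing-data sentence is not limited to any variable, so it governs the primary outcome as well.

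**The concern.** The two conditions for imputation are joined by 'and'. Read that way, the rule has three faults.

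1. **The trigger is the wrong way round.** Standard multiple imputation is justified when data are missing at random. The rule withholds it there and calls on it only where that assumption fails. Imputation under missing not at random needs an explicit model of how unseen values differ from seen ones, and the sentence does not tie the method to one.
2. **The trigger cannot be operated.** Whether data are missing not at random depends on the values that were not observed. The observed data cannot settle it, so the condition becomes a judgement that could be made after the results are known.
3. **The default conflicts with intention to treat.** Neglecting missing outcomes removes randomised patients from the comparison, and the exclusion of patients with incomplete forms or loss to follow-up does so a second time.

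At stake is the PONV comparison. If patients with and without PONV are lost at different rates in the two arms, the complete-case difference is biased, and the rule lets that stand up to 40% missing.

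**Working it through.** **Inputs.** From Sample size calculation: an assumption that esketamine may "reduce the PONV rate from 37.3 to 20" per cent, α = 0.05, power 90%, 139 per group. The test is two-sided (Statistical analysis). The total of 278 (Abstract) equals 2 × 139, so it shows no allowance for loss. The documents give no expected missing share, so 10%, 20% and 40% are assumed; 40% is the rule's own limit.

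**Step 1: reproduce the plan's figure.** With unpooled variance, n = (1.960 + 1.282)² × (0.373 × 0.627 + 0.20 × 0.80) / 0.173² = 10.507 × 0.3939 / 0.02993 = 138.3, so 139 per group. The pooled form gives 142. The sample size is not in dispute.

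**Step 2: power when missing outcomes are dropped**, even if they are missing completely at random. With n = 139 × (1 − m) and p̄ = 0.2865:

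power = Φ[(0.173 − 1.960 × se₀) / se₁], where se₀ = √(2 p̄(1 − p̄)/n) and se₁ = √(0.3939/n).

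At m = 0.40, n = 83.4, se₀ = 0.0700, se₁ = 0.0687, and power = Φ(0.52) = 0.699. At m = 0 it is 0.895.

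**Step 3: bias from informative missingness.** Assumptions: true PONV rate 37.3% in both arms; the same missing share m in both; missing completely at random in group F; in group E, the odds of being missing are OR times higher for patients with PONV. Let a and b be the probabilities of being missing with and without PONV in group E:

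0.373a + 0.627b = m, and [a/(1 − a)] / [b/(1 − b)] = OR.

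The complete-case rate in group E is then e = 0.373(1 − a)/(1 − m), and the spurious benefit is d = 0.373 − e.

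Example, m = 0.40 and OR = 3: a ≈ 0.565, b ≈ 0.302, e = 0.373 × 0.435/0.60 ≈ 0.271, d ≈ 0.102.

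Type I error is 1 − Φ[(1.960 se₀ − d)/se₁] + Φ[(−1.960 se₀ − d)/se₁], with se₀ and se₁ recomputed from 0.373 and e.

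| Missing share | n per arm | Power (Step 2) | Spurious benefit in points, OR 1.5 / 2 / 3 | Type I error, OR 1.5 / 2 / 3 |
|---|---|---|---|---|
| 0% | 139 | 0.895 | none | nominal |
| 10% | 125.1 | 0.861 | 1.0 / 1.7 / 2.7 | 0.053 / 0.059 / 0.072 |
| 20% | 111.2 | 0.819 | 1.9 / 3.3 / 5.3 | 0.060 / 0.082 / 0.132 |
| 40% | 83.4 | 0.699 | 3.8 / 6.5 / 10.2 | 0.081 / 0.143 / 0.292 |

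An odds ratio below 1 reverses the direction of the bias. If the mechanism were the same in both arms, there would be no spurious difference under this null scenario.

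**Step 4: what imputation can and cannot do.** Imputation under missing at random with no useful predictors would not remove the bias in Step 3. It helps to the extent that completed assessments and antiemetic use carry information about the missing outcome.

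**The case against.** **The wording may be loose rather than wrong.** The comma in the sentence leaves room for 'not completely at random', under which imputation would be orthodox. That reading does not rescue the rule, because everything up to 40% would still be neglected. Reading it as a free choice between neglect and imputation is worse, since the analyst would then choose.

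**Little may be missing.** Follow-up is three days and the first assessments fall within hours of surgery. This stands: 40% is what the rule tolerates, not a forecast. At 10% the illustrated bias is at most 2.7 points against a target difference of 17.3.

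**The power loss comes from absent data, not from the rule.** This also stands. A reader might take the fall to 0.70 as the harm that imputation would undo, but imputing a binary outcome recovers only part of it, mainly where partial PONV data exist. Worst-case bounds behave likewise. With equal missingness they are (1 − m) × 17.3 ± 100m points: 15.6 ± 10 at 10%, or 5.6 to 25.6, which keeps the direction of effect; and 10.4 ± 40 at 40%. Imputation does not narrow them.

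**Two further inferences are not supported.** One is that the imputation branch would give falsely reassuring results. The direction of bias is unknown, and imputation under missing at random is not in general worse than dropping cases. The other is that the trial has no sensitivity analysis. The article does not name one, but that is commonly left to an analysis plan, which is not shown.

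**Conclusion.** The rule is wrong as written and should be replaced. It neglects missing data up to 40% regardless of mechanism, makes imputation depend on a condition that observed data cannot establish, and pairs that condition with a method whose standard form assumes the opposite. It also conflicts with the article's intention-to-treat statement, and the exclusion of incomplete or lost patients compounds the conflict. These conclusions rest on the text alone.

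The size of the harm rests on assumptions. The bias is about 1 to 3 points at 10% missing and 4 to 10 points at 40%, if missingness is informative in one arm with an odds ratio of 1.5 to 3. About 83 patients per arm and power near 0.70 describe the permitted extreme. The true missing share is unknown and may be small, so the documents do not show that the PONV result will in fact be distorted.

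The other reasons for removing patients after enrolment, such as a change of anaesthesia method, raise a separate question that is not counted here.

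**What to change.** Replace the sentence, before unblinding, with one rule:

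1. Delete the 40% threshold and the requirement that data be identified as missing not at random.
2. Keep all randomised patients in the primary PONV analysis, in the arm to which they were allocated.
3. Classify a patient as positive if any completed assessment to 72 h is positive.
4. Multiply impute every outcome still undetermined, under missing at random and at any level of missingness. This includes patients whose completed assessments are all negative but who have a gap. The model should contain arm, centre, procedure, age, and PONV and antiemetic use at completed time points.
5. Address missing not at random in a delta-adjusted or tipping-point sensitivity analysis.
6. Reconcile the exclusion of patients with incomplete forms or loss to follow-up, and the overlapping dropout definition, with intention to treat.

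The cost is revised wording and a little more programming. No new data are needed. Intervals may be slightly wider, because the uncertainty of the imputed outcomes is carried into them.

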## Discussion

In recent years, the perioperative use of opioids has caused an opioid crisis and has become a major public health issue worldwide. Opioids have a multitude of acute side effects including pruritis, respiratory depression, nausea and vomiting postoperatively. Among them, PONV has already been proven to be associated with prolonged hospital length of stay, unexpected hospital readmissions, increased medical expenses and patient dissatisfaction with the perioperative experience [29, 30]. Thus, one of the key elements of the implementation of ERAS protocols is to help patients minimize opioid use, without negatively impacting perioperative pain management or recovery [31].

OFA is essentially the practice of intraoperative anaesthesia without the use of intraoperative opioids and has been proven to be a feasible technique for safe sedation. One strategy for OFA is to increase nonopioid adjuncts during the implementation of multimodal analgesia or balanced analgesia. However, a substitute agent that can fully replace opioids perioperatively has not been found, and whether OFA is beneficial and can improve short-term and long-term patient outcomes remains unknown.

Recently, esketamine has received wide attention for its potential implications in treatment-resistant depression. In addition to its antidepressant effect, esketamine could also be an effective anaesthetic and analgesic agent used for surgical anaesthesia.

According to a recent study on Chinese patients, the administration of esketamine as a relatively small dose was generally safe for anaesthesia without consideration of sex differences [32]. In fact, several advantages of esketamine in clinical anaesthesia have recently been proven. First, it creates less impairment on patients’ spontaneous breathing and airway reflexes as well as circulation stability due to an increase in sympathetic tone. In addition, Eberl et al. [17] reported that low-dose esketamine reduces the total amount of propofol necessary for sedation during ERCP while proving satisfactory sedative effects. Furthermore, many studies report that a combination of propofol with ketamine may result in a better quality of sedation and analgesia, with shorter recovery time, better satisfaction of patients and fewer respiratory or cardiovascular side effects [33]. Despite all these benefits, one widespread concern of esketamine is that it can produce psychotomimetic effects that may be associated with cognitive impairment [13].

In this trial, we hypothesized that OFA with esketamine could reduce the PONV rate after laparoscopic surgery based on several possible underlying mechanisms. On the one hand, it certainly reduced the consumption of opioids perioperatively, which has been proven to be one of the main risk factors for PONV [34]. On the other hand, esketamine is also known for its effective effects in maintaining spontaneous breathing and airway reflexes during anaesthesia; in addition, it can increase sympathetic tone and result in less hypotension and cardiac depression [35]. The reduced interference of esketamine on respiratory and circulatory systems during surgery also provides better conditions for ERAS in patients.

However, research on the advantages or disadvantages of esketamine in surgical anaesthesia remains deficient, and further randomized trials with larger sample sizes are urgently needed in this area. In this study, we also plan to investigate intraoperative circulatory stability as well as other recovery indices for esketamine in anaesthesia for laparoscopic appendectomy and cholecystectomy.

A limitation of our study could be that no patients in either group accepted pretreatment for PONV, in case it may cover the potential anti-PONV effect of esketamine. As a rescue regimen, we allowed the prescription of antivomiting agents postoperatively as needed, and the consumption of postoperative antivomiting agents was also recorded and analysed. Additionally, we defined side effects and cognitive dysfunctions according to the SIVA consensus statement for standardized definitions and terminology for sedation-related adverse events [36]. However, their clinical impact cannot be determined when a sedation specialist provides adequate rescue manoeuvres during such events.

In summary, the aim of our trial is to demonstrate that the synergy of esketamine and propofol reduces PONV as well as other short-term adverse events, thereby providing a better safety and satisfaction profile of ERAS for laparoscopic appendectomy and cholecystectomy.

## Trial status

The first patient was included on October 1, 2021. We expect to finalize the study in September 2022.

## Data Availability

Not applicable
